#### Waist–hip ratio

Waist and hip measurements are taken according to the WHO’s guidance. A tape measure is used to record the hip and waist circumference to the nearest centimetre.^52^ The waist–hip ratio is calculated by dividing hip and waist circumference.

### Biomarkers

#### HbA1c and cholesterol

Fasted capillary blood samples are collected to determine HbA1c (mmol/mol, %), estimated average glucose (eAG, mol/L) and full lipid profiles, including total cholesterol, low-density lipoprotein, high-density lipoprotein (HDL), triglycerides, non-HDL and cholesterol/HDL (mmol/L) assayed using a benchtop analyser (Alere Afinion AS100 Analyser, Alere, Stockport, UK).^53^

#### Blood pressure heart rate

Systolic and diastolic blood pressure (BP) and resting heart rate (HR) (Microlife BP A2 Basic, Gentle Technology, Microlife, Clearwater, FL, USA,) are measured three times with the participant at rest in the sitting position. The mean value is recorded.

#### Hair cortisol

Hair samples are collected by cutting a small tuft of hair close to the scalp to measure the stress hormone, cortisol, and analysed following a previously described protocol^54^ (online supplementary file 2).

#### Physical activity

Physical activity is measured by the self-reported International Physical Activity Questionnaire (IPAQ)^55^ and Activity Choice Index (ACI).^56^ Minute-by-minute physical activity data and heart rate are measured by the Fitbit Charge 2 for the study duration.

#### Sleep quality and quantity

The Fitbit Charge 2 estimates sleep quantity (hours/minutes) and quality (stages of sleep). Data are collected throughout the trial.

#### Dietary intake and eating behaviour

Four consecutive 24-hour-web-based dietary recalls, including at least 1 weekend day, are collected within 7 days of each visit using INTAKE 24.^57^ Psychometric measures of eating behaviour are assessed at each visit using the Three Factor Eating Questionnaire-51,^58^ the Problematic Eating Patterns Scale (unpublished scale), Eating in the Absence of Hunger Scale,^59^ Intuitive Eating Scale-2^60^ and the Binge Eating Scale.^61^

#### Well-being and quality of life

Quality of life and well-being are assessed using the 5-level EQ5D (EQ5D-5L)^62^ and the Warwick-Edinburgh Well-Being Scale,^63^ respectively.

#### Self-regulation

Self-regulation is measured using the Action Planning and Coping Planning Scales^64^ and Action Control Scale.^65^

#### Motivation

Satisfaction of psychological needs are assessed using the Basic Psychological Needs and Frustrations Scale.^66^ Quality of goal contents is assessed using the Goal Content for Weight Loss Maintenance Scale.^67 68^ Autonomous and controlled motivation are assessed using the Behavioural Regulation in Exercise Questionnaire (BREQ-3),^69^ Regulation of Eating Behaviour Scale (REBS)^70^ and Regulations for Weight Management Scale (adapted from the REBS).^70^

#### Self-efficacy

Self-efficacy is assessed using the Self-Efficacy for Weight Maintenance Scale.^71^

#### Emotion regulation and stress management

CB-emotion regulation and stress management constructs are measured using the Weight Focused Self-Criticism/Self-Reassurance Scale,^72^ Weight Focused External Shame Scale,^73 74^ the Compassion Engagement and Actions Scales,^75^ Body Image Acceptance and Action Questionnaire,^76^ Engaged Living Scale,^77^ Mindful Attention Awareness Scale,^78^ adapted Difficulties in Emotion Regulation Scale^79^ and Experiences Scales (decentering subscale only).^80^ Perceived stress is measured by the Perceived Stress Scale.^81^ Anxiety and depression are measured using the Depression & Anxiety Stress Scales.^82^

#### Demographics, weight history and participant traits

A profiling questionnaire, adapted from the DiOGenes study,^83^ is administered at baseline only to measure trait-specific moderators of WLM including the following demographics: age, gender, country, education, marital status, employment and income. Also, smoking and alcohol use and number of times giving birth are recorded. Weight history includes height, current and highest weight in the last 12 months, successful and unsuccessful WL attempts and strategies, and psychological impact of living in a food abundant environment (the Power of Food Scale).^84^ Self-determination traits are assessed using the Index of Autonomy Functioning^85^ and Aspirations Index,^86^ and self-regulation of appetite, hunger and satiety cues by the Intuitive Eating Scale-1.^87^ Relapse prevention capability is measured using an adapted Relapse Prevention Scale.^88^

### Process evaluation and user experience

Questionnaires adapted from the Technology Acceptance Model for Mobile Services (TAMM)^89^ are administered by email to assess reasons for engagement/dropout and user-experience (eg, perceived ease-of-use and adoption, perceived value, trust, acceptability and usability). Digital literacy is assessed at 1 month using the eHealth Literacy Scale (eHEALS).^90^ Twelve focus groups were conducted (four in each country) at 6 months, by independent researchers, to thematically explore contextual factors (eg, influence of wider social networks), user experience and the toolkit use context in the three countries.^91^ Metadata on reach (participant characteristics), dose, fidelity and engagement with the toolkit are extracted from log files (online supplementary file 2). Methods and analyses will be detailed in separate publications.

### Data analysis

The 2×2 factorial design will be used in a model to investigate links between outcomes, and the extent of mediation or moderation by covariates. For continuous outcomes, linear regression models will be used. The effects of different treatment arms will be presented with 95% CI of coefficients and p values. For analyses that do not meet model assumptions, outcomes will be transformed prior to inferential comparisons. For categorical outcomes, logistic regression or categorical response models such as ordinal or multinomial regression will be used. Treatment effects will be presented as ORs, 95% CIs and p values. Missing values will be imputed using multiple imputation as part of an intention-to-treat (ITT) analysis.

To determine the mechanisms that underlie intervention efficacy, linear models are used to test whether the treatment (independent variable) causes a change in the potential mechanisms of change (mediators), which, in turn, cause a change in the primary and secondary outcomes (dependent variables). Models also investigate the effects of covariates that may moderate the effect of the interventions. Although a repeated measures/mixed model might potentially detect treatment effects not apparent when 6-month and 12-month outcomes are considered separately, our choice was driven by the primary role of the 12-month outcome. To be considered worthwhile, a WL or maintenance effect of treatment must be detectable at 12 months, whatever might happen during the time interval between then and baseline. Because of this, we chose to define the primary outcome and its analysis at 12 months alone.

For the primary outcome of weight, we intend to present results from an analysis of completers, of compliant participants and of the ITT population. Baseline and last observation carried forward are likely to be optimistic for dropouts, implying full WLM. So, for these dropouts, we will examine analyses which assume regain of all or a range of proportions of the weight lost since highest weight (in the 12 months before enrolment, for which all participants have provided evidence). Again, assuming return to baseline may be optimistic, but we do not have values at the time of greatest weight. Accordingly, we plan multiple imputation based on the imputed weight changes described above, using also centre and gender. This is not available for other health outcomes, such as HbA1c or blood pressure.

Mediation is assessed where change in weight, as represented by a categorical endpoint (maintenance vs weight regain), is the dependent variable, intervention group is the predictor variable, and self-regulatory, emotion regulatory and other psychosocial variables are mediators. Hybrid models, combining latent and observed variables, may be specified to ensure sufficient power to conduct the analysis and to stay within the limits of sample size requirements. Model fit will be assessed using the χ^2^ goodness-of-fit test, Bollen’s incremental fit index (0.95) and the standardised root mean residual (0.08) values. Tests of mediation will be conducted using a resampling method. To test the significance of specific indirect effects of multiple mediators (total and specific for each mediator, using both normal theory and bootstrap procedures), a tool developed by Selig and Preacher^92^ will be used.

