### Assessments

The primary outcome is change in weight (kg) between baseline and 12 months (primary endpoint). Follow-up measures for WLM are completed at month 18 for comparability with other longitudinal studies.^22^ All physical measurements are taken after a 10–12 hour overnight fast by trained research staff. Measures are taken at all four time points (baseline, 6, 12 and 18 months) except HbA1c, lipids and hair cortisol (baseline and 12 months only) and process evaluation measures (1, 3, 6 and 12 months only). The study schedule and information for all measures is in online supplementary file 2.

10.1136/bmjopen-2019-029425.supp2Supplementary data

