### Primary outcome

#### Change in weight (kg) at 12 months from baseline

Body weight (±0.1 kg) is measured using a Seca 704 s instrument (SECA, Germany) in participants wearing light clothing. Participants are asked to weigh themselves at least twice weekly, in the morning after voiding and before eating using the Fitbit Aria scales for 18 months.

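### The mediation paragraph cuts weight change to maintenance versus regain, without a reason, although the preceding text tests mechanisms with linear models on the primary outcome in kg

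*Protocol article*

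**What the plan says.** - **Primary outcome.** Under Assessments: "The primary outcome is change in weight (kg) between baseline and 12 months (primary endpoint". The Primary outcome section repeats it as "Change in weight (kg) at 12 months from baseline". It is continuous.
- **Model by type of outcome (Data analysis, first paragraph).** "For continuous outcomes, linear regression models will be used". Also: "For categorical outcomes, logistic regression or categorical response models such as ordinal or multinomial regression will be used". Effects on categorical outcomes are to be shown as odds ratios.
- **Mechanisms (Data analysis, second paragraph).** The first step is given as "linear models are used to test whether the treatment (independent variable) causes a change in the potential mechanisms of change (mediators"). For the second step, from mechanism to outcome, the dependent variables are the trial's primary and secondary outcomes. The sentence names linear models only, and the primary outcome it refers to is in kg.
- **Mediation (Data analysis, last paragraph).** "change in weight, as represented by a categorical endpoint (maintenance vs weight regain), is the dependent variable". Intervention group is the predictor and the psychosocial variables are the mediators. Indirect effects are to be tested "total and specific for each mediator, using both normal theory and bootstrap procedures". The paragraph gives no reason for categorising weight and does not describe the analysis as additional.
- **Objective.** Mediators of weight loss maintenance are the third secondary objective (Study objectives and hypotheses).

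**The concern.** Two adjacent statements address the same question, how treatment acts on weight, with two different dependent variables. A reader cannot tell which result will be reported as the mediation finding for weight.

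The two choices are not equivalent. Cutting a continuous outcome in two discards information on every path that ends in weight. It may also change the scale. With a linear model for kg, the total effect is the sum of the direct and indirect effects, all in kg, and it connects to the primary result. With a logit-type model for a binary outcome, coefficients shift when mediators enter the model even without confounding, so the total and indirect effects are not on one scale.

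The article does explain why age, BMI and weight are categorised for subgroup analysis (Subgroup analysis section). It offers no such explanation for categorising the outcome here.

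**Working it through.** **Inputs from the article (Power calculations and sample size estimation).** Difference of 1.5 kg, d = 0.25, so the implied SD is 1.5/0.25 = 6 kg; 80% power; 250 per arm; about 1,000 participants at 12 months. The 5% level is stated in the HbA1c sentence. I assume that it is two-sided and also applies to weight.

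**Assumed, because the article gives no figure.** Weight change is roughly normal. The share of maintainers in the reference arm is varied from 20% to 80%. Mediator–weight partial correlations of 0.10, 0.15 and 0.20 serve as illustrations.

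**1. Reproduce the plan's figure.** n per arm = 2(1.960 + 0.842)²/0.25² ≈ 251, or 252 with the t correction, against 250 stated. Power at 250 per arm is 79.8%. The plan's figure reproduces.

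**2. Efficiency after a split.** For a normal outcome cut so that a proportion p falls on one side, the asymptotic relative efficiency is φ(z_p)²/[p(1 − p)].

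| Split | φ(z_p) | Relative efficiency |
|---|---|---|
| 50/50 | 0.399 | 0.159/0.25 = 0.64 |
| 30/70 | 0.348 | 0.121/0.21 = 0.58 |
| 20/80 | 0.280 | 0.078/0.16 = 0.49 |

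**3. Treatment-to-weight path.** With p₁ maintainers in the reference arm and a 0.25 SD shift, p₂ = Φ(z_p₁ + 0.25). Power is Φ[(p₂ − p₁ − 1.96·SE₀)/SE₁], with SE₀ pooled under the null and SE₁ unpooled. For p₁ = 0.50, p₂ = 0.599, SE₀ = 0.0445 and SE₁ = 0.0443, so power = Φ[(0.0987 − 0.0872)/0.0443] = 60.2%.

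| Maintainers, reference arm | 250 vs 250 | n per arm for 80% | 500 vs 500 (factorial margin) |
|---|---|---|---|
| kept in kg | 79.8% | 252 | 97.7% |
| 50% | 60.2% | 398 | 88.2% |
| 30% | 58.0% | 420 | 86.4% |
| 70% | 53.9% | 463 | 83.0% |
| 20% | 52.5% | 480 | 81.7% |
| 80% | 46.2% | 563 | 75.2% |

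**4. Mediator-to-weight path.** With N = 1,000, the expected test statistic is z = r√N/√(1 − r²), and power after the split is Φ(z·√efficiency − 1.96).

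| Assumed r | z in kg | Power in kg | Power after split (20/80 to 50/50) |
|---|---|---|---|
| 0.20 | 6.46 | over 99.9% | 99.5% to 99.9% |
| 0.15 | 4.80 | 99.8% | 92% to 97% |
| 0.10 | 3.18 | 89% | 60% to 72% |

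**5. Treatment-to-mediator path.** The mediators stay on their own scales whatever is done to weight, so this path loses nothing. An indirect effect is the product of the paths in steps 4 and 5, and only the first is weakened.

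**The case against.** The strongest reply is that there is no contradiction. The second paragraph of Data analysis gives a general approach for all outcomes, the first paragraph allows logistic and other categorical models, and the last paragraph can be read as a further analysis of maintenance status. Maintenance is the trial's own construct, and maintained versus regained is a legitimate quantity to study. This stands in part: the text never says that the binary endpoint replaces kg. But it does not say that it is additional either. The mechanism sentence names linear models only, and the loss of information remains unexplained.

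Several stronger readings are tempting and are not supported:

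- *The split is like dropping 36% to 51% of participants from the mediation analysis.* These percentages are one minus the efficiencies in step 2. They apply only to paths into weight, not to the indirect effect.
- *Mediation power falls from 80% to somewhere between 46% and 60%.* That is the total treatment effect between two single arms. The article gives no power for mediation, and on the factorial margins the fall is from 97.7% to between 75% and 88%.
- *The sentence on hybrid models admits low power because of the binary outcome.* It speaks of combining latent and observed variables within sample-size limits, which is a matter of model complexity.
- *The cut is arbitrary because no threshold is given.* The definition may be in the full protocol or analysis plan, so its absence from an article is not a finding.
- *The mediation result cannot be reconciled with the kg result.* The scale problem presumes a logit-type model. The mediation paragraph names no link, and its fit indices point to structural equation modelling.

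**Conclusion.** The point holds as an inconsistency with an avoidable cost. The article states two dependent variables for the mechanism analysis of weight and does not say which leads. The categorical one keeps about 64%, 58% or 49% of the efficiency on paths into weight at 50/50, 30/70 or 20/80 splits.

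For indirect effects, the consequence depends on the mediator–weight association. It is negligible at an assumed partial correlation of 0.20 and material at 0.10, where power for that path falls from 89% to between 60% and 72%. These figures rest on approximate normality, about 1,000 completers, and maintainer shares and correlations that the article does not supply. If a logit-type model is used, the indirect effects also do not decompose the kg effect.

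Mediation is a secondary objective. Nothing here touches the primary 12-month test, the sample size or trial conduct.

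**What to change.** In the mediation paragraph of Data analysis, replace the definition of the dependent variable with wording such as:

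> The dependent variable of the main mediation model is weight change in kg from baseline to 12 months, analysed as continuous in a linear model with adjustment for baseline weight. Indirect effects are reported in kg with bootstrap confidence intervals. Maintenance versus regain is analysed as a supplementary binary endpoint, with its model stated.

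Then make the mechanism sentence earlier in the section agree with it. If the authors want the categorical endpoint to lead, both places should say so and give the reason.

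The change costs wording only. Weight is already measured at baseline and 12 months, bootstrap inference is already planned, and keeping the binary analysis as supplementary means that nothing is given up.

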### Subgroup analysis

Interactions between condition factors and baseline participant groupings (centre, gender, age, BMI at entry, % WL at entry) will be prioritised as a priori subgroup analyses in the primary and secondary outcomes. Age, BMI and weight will be analysed as categorical variables to avoid assumptions of linearity (or the complexity of fitting polynomial terms) and for ease of presentation. These pre-planned analyses will be conducted by the inclusion of appropriate interaction terms in the regression models. Where interactions are significant, results for each subgroup will be reported. This will mitigate the problems of multiple testing due to many subgroup comparisons. We recognise that statistical power in subgroups will vary with sample size and provide a plot of detectable effect size versus sample size for reference (figure 3).

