### Study objectives and hypotheses

The effectiveness of long-term evidence-based digital interventions and strategies to support WLM is limited.^45^ The study’s primary objectives are to evaluate whether using a new digital toolkit is effective for WLM by improving (1) self-regulation and motivation, (2) emotion regulation or (3) these factors in combination, compared with (4) control (generic toolkit content, regular self-weighing and Fitbit use), in 1627 participants at three European centres. We hypothesise that the combined intervention will be more effective for WLM compared with the self-regulatory or emotion regulatory interventions alone, which will also be more effective than the control group.

Secondary objectives are to determine (1) how the intervention affects health markers (eg, levels of glycated haemoglobin (HbA1c)) and body composition; (2) examine the intervention impacts on physical activity, sleep, dietary intake, depression, anxiety, stress, quality of life and well-being; (3) examine mediators of WLM, such as self-regulation (eg, planning capacity), motivation (eg, autonomous motivation) and emotion regulation processes (eg, self-compassion); (4) analyse baseline moderators (eg, gender, body mass index (BMI)) to identify participants who are more responsive to motivational and behavioural self-regulatory or CB-emotion regulatory approaches for WLM; (5) conduct quantitative and qualitative assessment of user-experience, acceptability, engagement and dropout; (6) examine intervention cost-effectiveness; and (7) to determine the efficacy of individualised feedback from data on physical activity self-tracking.

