### Power calculations and sample size estimation

Power calculations were based on the primary outcome (weight change). To detect a difference between treatment arms of >1.5 kg body weight gives a (Cohen's) d value of 0.25.^22^ For 80% power, comparing more than two groups requires a sample size of 250 per trial arm. To detect an effect size of 0.25 SD units for HbA1c, 245 participants in each trial arm gives 80% power, at 5% significance. Assuming 38% dropout,^83^ a sample size of 1600 (533 per centre) is needed to achieve a sample of 1002 (334 per centre, ~250 per trial arm) participants at 12 months.

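### Age, BMI and weight are categorised in the interaction tests that decide which subgroup results are reported; if moderation is roughly linear, an 80% test falls to about 54–61%

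*Protocol article*

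**What the plan says.** The Subgroup analysis section of the protocol article says that interactions between the condition factors and "baseline participant groupings (centre, gender, age, BMI at entry, % WL at entry) will be prioritised as a priori subgroup analyses", for the primary and secondary outcomes. It then fixes the form of the continuous moderators: "Age, BMI and weight will be analysed as categorical variables to avoid assumptions of linearity (or the complexity of fitting polynomial terms", with ease of presentation as a second reason. The test is also fixed: "These pre-planned analyses will be conducted by the inclusion of appropriate interaction terms in the regression models". The reporting rule follows: "Where interactions are significant, results for each subgroup will be reported".

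The section acknowledges that power in subgroups depends on their size and points to a plot of detectable effect against sample size (Figure 3, not shown in the text available). It gives no number of groups, cut-points, interaction effect size or interaction power.

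The moderator question is secondary objective 4 under Study objectives and hypotheses: to "analyse baseline moderators (eg, gender, body mass index (BMI)) to identify participants who are more responsive".

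**The concern.** Categorising is a stated method here, with stated reasons, and not a detail left open. Neither reason requires categories in the test. A smooth curve also avoids assuming a straight line, and it does so without treating everyone inside a group as alike and placing jumps at the cut-points. Ease of presentation is a reason to group the estimates in a table or plot, which can be done after a test on the continuous scale.

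The choice matters because the interaction test decides whether subgroup-level results appear. BMI is one of the two examples named in the moderator objective. The Power calculations section sizes the trial for differences between arms and claims no power for interactions, so there is no stated margin to give up.

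There is also a textual mismatch. The list of moderators names percentage weight loss at entry, but the sentence on categories says weight. These are different variables, and as written the form of percentage weight loss is not given.

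**Working it through.** **Inputs from the article (Power calculations and sample size estimation).** "To detect a difference between treatment arms of >1.5 kg body weight gives a (Cohen's) d value of 0.25", so the implied SD is 1.5 / 0.25 = 6.0 kg. "For 80% power, comparing more than two groups requires a sample size of 250 per trial arm". The 5% significance level is stated for HbA1c ("245 participants in each trial arm gives 80% power, at 5% significance") and is taken here as two-sided for weight as well. The expected number at 12 months is 1002, or 501 per level of each factor.

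**Assumptions, because the article gives no figure.** The moderator is normal, moderation is linear, groups are of equal size and number 2 to 5, and the continuous 1-df test has 80% power as the reference.

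**Step 1: the plan's own figure.** n per arm = 2(1.960 + 0.842)² / 0.25² = 251.2, or 252 with the t distribution, against the stated 250. Power at 250 per arm is 79.8%. The stated figure reproduces.

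**Step 2: reference interaction.** For one two-level factor and N = 1002, a noncentral F test on 1 df reaches 80% power at noncentrality λ = 7.86. With the moderator in SD units, λ = b²N/4. So b = √(4 × 7.86 / 1002) = 0.177 SD, or 0.177 × 6.0 = 1.06 kg difference in slope per SD of the moderator.

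**Step 3: categorise.** Cutting a normal variable into k groups multiplies λ by the share R of its variance lying between groups, and the test then has k − 1 df.

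| Equal groups | R | λ × R | df | Power | Relative loss from 80% |
|---|---|---|---|---|---|
| 2 | 0.637 | 5.01 | 1 | 60.8% | 24% |
| 3 | 0.793 | 6.24 | 2 | 60.0% | 25% |
| 4 | 0.861 | 6.77 | 3 | 57.2% | 28% |
| 5 | 0.897 | 7.05 | 4 | 54.1% | 32% |

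More groups keep more information but spend it on extra degrees of freedom, so power does not recover. A simulation with 4000 replicates gave 80.0% for the continuous test and 60.4%, 60.3% and 58.3% for 2, 3 and 4 groups.

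**Step 4: vary the assumptions.**
- Reference power: with 2 to 5 equal groups the relative loss is 31–45% from a 50% reference and 18–24% from a 90% reference.
- Uneven cuts at the 80% reference: 56.6% power for a 30/70 split, 50.0% for 20/80, 57.9% for 50/30/20.
- Four arms tested jointly in place of one factor: power falls from 80% to 58.6%, 56.8%, 52.9% and 49.0% for 2 to 5 groups.

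**Step 5: compare with a spline instead of a straight line.** At λ = 7.86 with linear truth, a joint test of a continuous curve has 70.8% power on 2 df and 64.4% on 3 df. Three equal groups then lose 1 − 60.0/70.8 = 15%, or 1 − 60.0/64.4 = 7%.

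**Step 6: other shapes, same total noncentrality.**

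| True moderation | Linear term | 2 groups | 3 groups | 4 groups |
|---|---|---|---|---|
| Step at the median | 61% | 80% | 52% | 64% |
| Step at the lower tertile | 58% | 51% | 71% | 51% |
| U-shape | 5% | 5% | 20% | 26% |

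For the steps, categories gain most when a cut falls on the true threshold. For a U-shape, a straight line has no power and three or four groups have little.

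**The case against.** The strongest reply is that the calculation assumes the linear truth that the authors declined to assume, so a continuous linear test is bound to win. That stands as a limit on the size. Step 6 shows that the direction can reverse, and Step 5 shows that against a test which also avoids linearity the gap is modest. A reader might infer that the plan simply loses about a quarter of its power for moderators. The article does not support that without conditions, because the figure needs an assumed number of groups, distribution, shape and reference power.

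A reader might also infer that a step function is a stronger assumption than linearity. Neither model contains the other, so this cannot be said in general. The comparison that does hold is with a smooth curve, which meets the authors' aim without needing the cut-points to be right.

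A third tempting inference is that real moderators will be hidden. The reporting rule covers only results within subgroups. It does not say that interaction estimates or tests go unreported, and the Data analysis section separately plans models of moderating covariates with no restriction to categories. Centre and gender, two of the five groupings, are categorical in any case.

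Finally, the choice is a reasoned one, the article admits that subgroup power varies, and group numbers and cut-points may properly sit in an analysis plan that is not shown. Their absence is therefore not criticised here. But the caveat as worded concerns subgroup size, not information lost by grouping, and the decision to categorise within the test is fixed in the article.

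**Conclusion.** The point holds in conditional form. For a roughly normal moderator with roughly linear moderation, 2 to 5 equal groups reduce an 80% interaction test to about 54–61%. Against a 2-df spline at 71% the loss with three groups is about 15%, and against a 3-df spline at 64% about 7%. If the true effect is a step at a chosen cut-point, categories can do better than a straight line.

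The recommendation does not depend on linearity being true. Both stated reasons for categorising are met by a continuous curve in the test and categories in the display. The consequence is confined to the a priori subgroup analyses for age, BMI and weight or weight loss. The primary main-effect comparison is untouched and its sample size reproduces. The mismatch between weight and percentage weight loss at entry is real but minor; weight may be shorthand for the variable named in the preceding list.

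**What to change.** Test each factor-by-moderator interaction with age, BMI at entry and percentage weight loss at entry kept continuous. Use a pre-specified restricted cubic spline, for example 3 knots with a joint 2-df interaction test, so that linearity is not assumed. Show the estimates in pre-set categories for presentation only. Make the sentence on form name the same variable as the list of moderators.

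The cost is a sentence or two of text and a few lines of code, with no new data. The downside is one extra degree of freedom compared with a linear term (71% against 80% power if moderation is exactly linear) and a plot to explain.

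### Showing subgroup results where an interaction is significant limits multiplicity only in part, and makes the results shown selective and exaggerated on average

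*Protocol article*

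**What the plan says.** All of this is in the Subgroup analysis section of the protocol article unless another section is named.

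- **What is tested.** Interactions between the condition factors and "baseline participant groupings (centre, gender, age, BMI at entry, % WL at entry) will be prioritised as a priori subgroup analyses", with the scope given as "in the primary and secondary outcomes".
- **How.** "These pre-planned analyses will be conducted by the inclusion of appropriate interaction terms in the regression models".
- **What is shown.** "Where interactions are significant, results for each subgroup will be reported. This will mitigate the problems of multiple testing".
- **The reason given, in full.** "This will mitigate the problems of multiple testing due to many subgroup comparisons".

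The section also acknowledges that power in subgroups varies with their size and refers to a plot of detectable effects. It gives no threshold for the interaction tests and does not call these analyses exploratory; it describes them as planned in advance. Data analysis adds that "The 2×2 factorial design will be used in a model to investigate links between outcomes", so there are two condition factors: self-regulation with motivation, and emotion regulation.

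**The concern.** The safeguard against multiplicity is a display rule that depends on significance, which raises two separate problems.

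1. **Error across tests.** Requiring a significant interaction before looking within subgroups limits the within-subgroup tests. It does nothing about the number of interaction tests, and that number is not small.
2. **Selection.** If subgroup estimates appear where the interaction was significant, readers see the contrasts that chance has helped along. They do not see the intervals that would show what has been ruled out elsewhere.

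This matters because identifying who responds better to which approach is a stated secondary objective (Study objectives and hypotheses, item 4). Potential outcomes and impact says the secondary analyses will inform more personalised interventions. A chance interaction on weight could be carried forward into that work.

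**Working it through.** **The plan's own figures.** Power calculations and sample size estimation gives 1.5 kg as d = 0.25, so the implied SD is 1.5 / 0.25 = 6 kg. For two arms at two-sided 5% and 80% power, n = 2 × (1.96 + 0.84)² / 0.25² ≈ 251 to 252 per arm. The plan says 250, which gives 79.8% power, so the figure reproduces. Expected completers are 1600 × 0.62 = 992 (the plan says 1002). I use 1000 below. The subgroup section states no error rate to reproduce.

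**Assumptions the document does not supply.** Each interaction is tested at 5%. The tests are independent. In the simulation, age, BMI and % weight loss have three levels each, centre has three and gender two, and levels are of equal size.

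**Chance of at least one false interaction on weight**, 1 − 0.95^k:

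| Interaction tests | k | Chance |
|---|---|---|
| One joint test per grouping | 5 | 22.6% |
| 5 groupings × 2 factors | 10 | 40.1% |
| Also grouping × the two-factor interaction | 15 | 53.7% |

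A simulation of the 10-test case with 1000 completers and no true effects gave 40.3%, with about 0.5 false interactions per trial. Each secondary outcome examined adds another set of tests.

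**What the interaction requirement achieves.** In the same simulation:

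- testing every subgroup effect directly gave at least one significant subgroup effect in 65.9% of null trials;
- requiring a significant interaction first reduced this to 33.8%.

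The requirement roughly halves the rate of false claims and leaves it well above 5%.

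**Exaggeration after selection, two equal subgroups.**

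- The SE of the difference between subgroup effects is 4 / √1000 = 0.126 SD.
- With no true difference, the mean absolute difference given |z| > 1.96 is 2 × φ(1.96) / 0.05 = 2.34 SEs, or 0.296 SD (about 1.8 kg). Without selection it is 0.80 × 0.126 = 0.101 SD (about 0.6 kg).
- The SE of the overall effect is 2 / √1000 = 0.063 SD. With no true effect, the larger absolute subgroup estimate then averages 0.80 × 0.063 + 0.296 / 2 = 0.198 SD, matching the simulated 0.20. Without selection it is 0.050 + 0.050 = 0.101 SD.

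The unselected figure is needed as a comparator, because the largest of several estimates exceeds the truth on average even when nothing has been selected. Most extreme subgroup estimate, in SD units (kg at SD 6):

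| True effect | Levels | No selection | After a significant interaction |
|---|---|---|---|
| 0 | 2 | 0.10 (0.6) | 0.20 (1.2) |
| 0 | 3 | 0.15 (0.9) | 0.27 (1.6) |
| 0.25 in every subgroup | 2 | 0.30 (1.8) | 0.40 (2.4) |
| 0.25 in every subgroup | 3 | 0.34 (2.1) | 0.45 (2.7) |

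The right-hand column comes from the simulation. The three-level unselected values come from a separate direct simulation of three independent subgroup estimates, each with SE 2 / √(1000/3) = 0.110 SD. Selection on the interaction does not bias the average effect across subgroups. It exaggerates the spread between them, and so the most extreme one.

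**Power.** For a two-level interaction of 0.25 SD, z = 0.25 / 0.126 = 1.98, so power at 5% is about 51%. At 0.05 / 10 = 0.005 it is about 20%.

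**The case against.** Much of the case on the other side stands.

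- **The protocol claims mitigation, not control**, and only of the problem arising from many subgroup comparisons. The fall from about 66% to 34% shows that this is partly true. Testing pre-specified interactions is the accepted approach, so the sentence needs qualifying, not deleting.
- **A reader might infer that non-significant interactions will be withheld.** The text does not say so. It makes the breakdown by subgroup conditional and is silent on interaction p values. But the claim that the rule mitigates multiple testing makes sense only if that breakdown is not shown otherwise, so conditional display of estimates is a fair reading.
- **A reader might infer that false or inflated claims are bound to follow.** They are not. In the 10-test case about 60% of null trials would show no significant interaction on weight, and exaggeration is an average tendency.
- **The threshold and any adjustment may be in a fuller plan.** Their absence from an article is therefore no finding. The point rests on the display rule, which the article does state; adding a threshold would not remove the selection.
- **Formal adjustment is a trade-off.** At Holm's first step over 10 tests, power for a 0.25 SD two-level interaction falls from about 51% to about 20%. An exploratory label is equally defensible.
- **Categorising the moderators is not an error here.** The section gives reasons: "Age, BMI and weight will be analysed as categorical variables to avoid assumptions of linearity", and ease of presentation. Any loss of efficiency depends on linearity and on a number of categories the article does not state.

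**Conclusion.** The point holds as a moderate one about reporting. Display tied to a significant interaction reduces false subgroup claims but leaves about a 40% chance of at least one false interaction on weight with 10 tests, or about 23% with five joint tests. The contrasts that pass are exaggerated on average: with no true effect, the most extreme subgroup estimate is around 1.2 to 1.6 kg, against 0.6 to 0.9 kg without selection.

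The error rates assume 5% per test and independent tests; dependence between the groupings would change them. The kilogram figures also assume 1000 completers, the implied SD of 6 kg, equal-sized levels and the assumed number of levels. The primary analysis of weight at 12 months is not affected. The documents do not support saying that null interaction tests will be concealed or that spurious claims are certain.

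**What to change.** 1. For the primary outcome, report effect estimates with 95% CIs and interaction p values for all five pre-specified groupings whatever the p value, for example in a forest plot.
2. State how many interaction tests were done.
3. Label the subgroup analyses of primary and secondary outcomes exploratory. Adjusting the primary-outcome interaction tests for multiplicity is an optional alternative.
4. Qualify the sentence on mitigation. Suggested wording: 'Testing interactions first limits the number of within-subgroup comparisons; it does not control the error rate across the interaction tests, and subgroup findings will be interpreted accordingly.'

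The cost is one more figure, a few sentences, and more cautious subgroup claims. No new data are needed and the primary analysis does not change.
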